## Abstract

**Background:**

Medication and behavior therapy are the conventional treatments for attention deficit hyperactivity disorder (ADHD), but they have limitations for preschool children. Evidence suggests that pediatric *tuina*, which is a modality of traditional Chinese medicine, might have beneficial effects on this condition.

**Objective:**

To assess the feasibility of conducting an RCT in terms of recruitment, use, and acceptability of the parent-administered pediatric *tuina* for ADHD symptoms in preschoolers.

**Methods:**

It is a single-center, two-arm, parallel, open-label, pilot randomized controlled trial (RCT). Sixty children with pre-specified ADHD symptoms (hyperactivity, anxiety, and sleep disturbance) together with one of their parents will be recruited and randomized into two groups at a 1:1 ratio. Parents in the parent-administered *tuina* group (intervention group, *n* = 30) will attend an online training program to learn pediatric *tuina* skills for ADHD symptoms and conduct this treatment on their children at home. Parents in the parent-child interaction group (comparison group, *n* = 30) will attend an online training about progressive muscle relaxation exercise and do this exercise with their children at home. Additional teaching materials will be provided to the participants in both groups. Both interventions should be carried out every other day during a 2-month treatment period, with each time around 20 min. Assessment will be performed at baseline, week 4, and week 8. The primary outcome measure is the Swanson, Nolan, and Pelham parent scale; the secondary outcomes include preschool anxiety scale, children’s sleep habits questionnaire, and parental stress scale. A process evaluation embedded within the outcome evaluation will be performed. Differences in the scale scores and test parameters between groups will be examined using a linear mixed-effects model. Qualitative data will be analyzed using thematic content analysis, facilitated by QSR NVivo.

**Discussion:**

This study will provide evidence on the acceptability and feasibility of pediatric *tuina* for ADHD in preschool children. The process evaluation will help to better understand the facilitators and barriers of the intervention functioning.

**Trial registration:**

The study was registered at ClinicalTrials.gov (Identifier: NCT04237259) on 14 February 2020.

Protocol version: 2; date, 23 June 2020

## Background

Attention deficit hyperactivity disorder (ADHD) is a prevalent neurobehavioral disorder of childhood period, which is characterized by chronic symptoms of children’s developmentally age-inappropriate, undesirable features and can be accompanied by academic and behavioral problems [1]. The overall incidence rate in children aged from 4 to 17 years in the USA was approximately 10.2% in 2015-2016, and the prevalence of diagnosed ADHD children in the USA has a continued significant increase in the past 20 years [2]. Children diagnosed with ADHD usually suffer from negative social and academic problems [3, 4], and more than half of them have ADHD comorbidities (e.g., anxiety, depression) [5, 6]. Moreover, as a chronic medical condition, ADHD symptoms may persist into adulthood [7–9].

Medication therapy and behavior therapy are recommended by the American Academy of Pediatrics (AAP) for ADHD [10]. Medication has a beneficial and rapid effect on ADHD core symptoms, but the effect does not maintain if the treatment discontinues. Besides, medication treatment, both stimulants, and non-stimulants may lead to potential adverse side effects [10–12]. Medication has a beneficial and rapid effect on ADHD core symptoms, but the effect does not maintain if the treatment discontinues. Besides, medication treatment, both stimulants, and non-stimulants may lead to potential adverse side effects [10]. Evidence-based behavioral treatments are strongly recommended for ADHD children of all ages. It provides parents with more chances to interact with their children. However, some factors limit the popularization of this therapy, such as the high cost, high family involvement, parents’ learning abilities, and the lack of standardized training patterns [10, 13]. Complementary therapies are also commonly used by children and adolescents with ADHD symptoms [14], and pediatric *tuina* is one of the complementary therapies.

Pediatric *tuina*, which is also called traditional Chinese medicine (TCM) pediatric massage or pediatric *anmo*, is a special modality of TCM therapies. It is a manual intervention for preventing and treating medical conditions in children based on TCM theories and previous experience. Different from other massage types, the body part to be treated by pediatric *tuina* could be a point, a line, a circle, or an area; thus, the corresponding manipulations are more complex. Commonly used *tuina* techniques include pushing, circular rubbing, nipping, kneading, pushing, arc-pushing, twisting, and rotating. Pediatric *tuina* is usually used for asthma, respiratory infection, congenital muscular torticollis (CMT), diarrhea, constipation, anorexia, atopic eczema, and other medical conditions in infants and children [15–21]. In the perspective of TCM, ADHD symptoms are associated with the disharmonious situation between *yin* and *yang* of a body. An ancient TCM literature—“Ling Shu·The Application of the Needles”—recorded relevant symptoms as follows: “Double *yang* persons, their spirit is easily excited, and their *qi* proceed easily, they are fervid and lofty, speak well and fast. When walking they raise their feet high.” Most researchers believe that the pathogenesis of ADHD is the abnormal exuberance of *yang*, which can be relieved by specific approaches of massage [22, 23], and the corresponding principle is to adjust the excess, deficiency, and inter-impairment of *yin* and *yang* to return to the balanced state. *Yin* and *yang* are mutual rooting and may induct, contain, transform to each other, which explains why *yang* syndrome could comprise some comorbidities like anxiety disorders, oppositional defiant disorder, psychomotor inhibition, and intermittent explosive disorder (Fig. 1).

**Fig. 1 Fig1:**
[figure not shown]
Illustration of the pathological mechanism of ADHD based on TCM theory

Parent-administered interventions attempt to enhance a parent’s understanding of child behavior management and the quality of the parent-child interactions, with the ultimate goal of optimizing the child’s developmental course [24]. A systematic review and meta-analysis of non-pharmacological interventions for ADHD found that psychological treatments administered by parents showed the largest effects among 54 randomized controlled trials (RCTs) for preschool children in terms of ADHD symptoms improvements [25]. A recent RCT of a dual-parent and trainer-delivered *qigong* massage intervention for young children with autism indicated that the parent-delivered massage provided effective early intervention for autism that was feasible for delivery at home [26]. Hence, the combination of parent-administered intervention mode and pediatric *tuina* might be a cost-effective and feasible way of treating ADHD symptoms.

Studies have been done to examine the effects and safety of complementary therapies on ADHD. Catalá-López and colleagues conducted a systematic review to compare the efficacy and safety of pharmacological, psychological, and complementary and alternative therapies for ADHD stressed that high-quality studies on multiple treatments for ADHD in children and adolescents are urgently needed [27]. Chen and colleagues carried out an RCT on using TCM acupressure therapy for treating ADHD in children, leading to a conclusion that TCM acupressure therapy had better effects than *Ritalin* on ADHD symptoms with higher acceptability [28]. Recently, Chen and colleagues performed a systematic review of using massage therapy for ADHD in children and adolescents, suggesting that massage seemingly has beneficial effects for improving ADHD symptoms However, the methodological quality of the included clinical trials was generally poor. Limitations include unclear randomization and allocation concealment methods, incomplete reporting of outcome data, a lack of validated outcome measures, and a high risk of biases correlated to a failure to blind participants and outcome assessors [29]. Further rigorously designed clinical trials are warranted to assess the effects of pediatric *tuina* on ADHD. Furthermore, there is no RCT conducted to test the feasibility and effects of parent-administered pediatric *tuina for* ADHD. Our team has demonstrated that it is feasible to train patients to perform self-administered acupressure for insomnia [30], knee pain [31], and stress [32] by a short training program. This pilot study will test the feasibility of training parents to conduct *tuina* on their children. Therefore, we designed this pilot study to explore the feasibility of parent-administered pediatric *tuina* for ADHD in preschoolers.

## Objectives

The primary aim of the pilot trial is to assess the feasibility of parent-administered pediatric *tuina* for ADHD symptoms (hyperactivity, anxiety, and sleep disturbance) in preschool children for a further fully powered RCT. Specifically, the objectives are the following:
To test the feasibility of the study design (such as participant recruitment, participants’ compliance, and data collection procedures).To access the use and acceptability of parent-administered pediatric *tuina* intervention.To evaluate the adverse events of the parent-administered pediatric massage for both preschool children with ADHD symptoms and their parents.To compare the preliminary effects of parent-administered pediatric *tuina* with parent-child interaction training control intervention.

## Methods

The present protocol has been registered within ClinicalTrials.gov (Identifier: NCT04237259) and is being reported in accordance with the reporting guidance provided in the Standard Protocol Items: Recommendations for Interventional Trials (SPIRIT) statement [33] (see checklist in Additional file 1). The final study report will be prepared in accordance with the reporting guidance provided in the CONSORT extension for reporting pilot randomized controlled trials [34, 35].

### Trial design

This study is a single-center, two-arm, parallel, open-label, pilot randomized controlled trial. Participants (parent-child pairs) will be distributed into the intervention group and the control group at a 1:1 ratio. Parents in the intervention group (*n* = 30) will receive a training of parent-administered pediatric *tuina* and perform manipulations on their child. Parents in the active control group (*n* = 30) will be given an online training session about the skills of interacting with their children and a progressive muscle relaxation exercise. Treatments as usual (TAU) of the preschoolers in both groups will not be intervened during the treatment period.

This study includes a feasibility phase, which is expected to be the first 2 months of data collection treatment period with around eight parent-child pairs. The feasibility stage is designed to preliminary test the logistics of the intervention delivery, and to undertake an early evaluation of the study design of the whole pilot trial.

### Participant timelines

The treatment period will be 8 weeks. Outcomes will be measured at 3 time points: baseline, week 4, and week 8. A CONsolidated Standards of Reporting Trials (CONSORT) flow diagram demonstrates the procedure of the trial, including the recruitment, allocation, and intervention (Fig. 2). A Standard Protocol Items: Recommendations for Interventional Trials (SPIRIT) diagram shows the schedule of enrollment, intervention, and assessment (Table 1).

**Fig. 2 Fig2:**
[figure not shown]
CONSORT flow diagram

**Table 1 Tab1:**
[figure not shown]
SPIRIT diagram

### Study setting

Participants will be recruited at Shandong University of Traditional Chinese Medicine Affiliated Hospital, which is a tertiary A hospital with a pediatric *tuina* clinic center and a pediatric *tuina* teaching base. The hospital is located in Jinan City, Shandong Province, China.

### Subjects and recruitment methods

This study will recruit 60 preschool children with ADHD symptoms (hyperactivity, anxiety, and sleep disorders) together with their parents. The methods of recruitment are as follows:
Flyers and posters in the affiliated hospitals of the universityAdvertisement through mass media, including newspaper and radioPoster through social media, including WeChat and Weibo

Children and their parents who are interested in participating will be screened according to the eligibility criteria via an online meeting. The researcher who is responsible for recruitment will explain the procedure of the study to the subjects’ parents. Parents will be required to sign the informed consent before participating in this study if they are eligible.

### Sample size

There are few published guidance concerning how large the sample size a pilot study should be. “Rule of 12” for continuous variables recommends that at least 12 participants for pilot studies with the primary focus of estimating average values and variability for planning larger subsequent studies. This size is practical for most early-stage researchers within a single center while still providing valued preliminary information [36]. It has been proposed that a sample size ranged from 10 to 40 each group is sufficient to assess the adequacy in providing a precise estimate of the between-group effect size. Assuming a 25% dropout rate, the total sample size will be 60 (*n* = 30 in the intervention group, *n* = 30 in the active control group). A sample size of at least 30 participants in each group will help to yield a confidence interval whose lower limits can help define the range of plausible values for subsequent power analysis [37]. Such a sample size is considered to be sufficient to provide the preliminary data required to test the feasibility, acceptability, and effects of parent-administered pediatric *tuina* for preschool children and assess the study design to provide instructive information and guidance to the further fully power study.

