## Data analysis and management

### Statistical analysis

Descriptive statistics for sociodemographic variables and clinical variables will be presented. Data will be presented as mean and standard deviation. The feasibility outcomes will be presented as percentage. The SNAP scores between the intervention group and the active control group in week 4 and week 8 will be compared using a linear mixed-effects model. Other analyses include using a linear mixed-effects model to compare the SNAP (for measuring ADHD symptoms), PAS (for measuring anxiety), CSHQ (for measuring sleep disturbance), and PSS (for measuring parental stress) in the intervention group with the control group at all assessment time points. To estimate the changes with time in each group, the repeated measures ANOVA will be used. The effect sizes will be estimated using between-group mean difference divided by a pooled standard deviation.

The analyses will be based on the intention-to-treat approach. Completer analysis will be a secondary analysis. Completer is defined as those who have attended all lessons, practiced the pediatric *tuina* or parent-child interaction training at least 3 times per week during the treatment period, and completed assessment time point. As the sample size is underpowered, all analysis will be presented with 95% confidence intervals to inform the precision of the results. Since data at the pilot stage is preliminary, it should be treated with caution.

All qualitative data, including interview transcriptions, text from self-report questionnaires, and content of parent logbooks, will be analyzed using thematic content analysis, facilitated by NVivo (QSR, Melbourne, VIC). Adaptations and rationale behind all reported changes to the intervention will also be listed, analyzed, and summarized. All interviews will be audio-recorded and transcribed verbatim. The transcripts will be verified for accuracy against the sound files and revisions will be made as appropriate. Any identifiable remarks will be anonymized before transcripts being imported into NVivo.

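### The sample-size text relies on at least 30 per group, but its own 25% dropout leaves 22-23 at week 8, where the lower confidence limit is usable for planning only if the observed effect exceeds about 0.6 SD

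*Protocol article*

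**What the plan says.** The Sample size section of the protocol article cites two rules of thumb. One recommends "at least 12 participants for pilot studies with the primary focus of estimating average values and variability". The other holds that "a sample size ranged from 10 to 40 each group is sufficient" for estimating the between-group effect size. It then sets the number: "Assuming a 25% dropout rate, the total sample size will be 60", split 30 and 30. The next sentence gives the purpose: "A sample size of at least 30 participants in each group will help to yield a confidence interval whose lower limits". Of those limits it says that they "can help define the range of plausible values for subsequent power analysis". The section ends by calling the size "sufficient to provide the preliminary data required to test the feasibility, acceptability, and effects" of the intervention. No number expected after dropout, no expected effect size and no interval width is stated.

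Under Trial design, parent-child pairs "will be distributed into the intervention group and the control group at a 1:1 ratio". The Statistical analysis section plans a linear mixed-effects model by intention to treat, a secondary completer analysis, 95% intervals throughout, and effect sizes in pooled-SD units. It introduces the intervals with the words "As the sample size is underpowered".

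**The concern.** The figure of 60 is presented as already containing the dropout allowance, yet the next sentence credits the design with at least 30 per group. Thirty is the most that can be enrolled in each arm, so any loss takes the trial below the number relied on. The width of an interval depends on the data analysed, and an allowance for dropout has a purpose only if precision is judged after it.

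The interval is given one planning use: its lower limits should inform the power analysis of the main trial. If the limit is zero or negative, no sample size follows from it. The team would then have to improvise, most likely by falling back on an imprecise point estimate.

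**Working it through.** **Inputs.** From Sample size: 60 in total, 30 per arm, 25% dropout, and the per-group numbers 10, 12, 30 and 40. From Trial design: 1:1 allocation. From Statistical analysis: 95% intervals and a standardised mean difference. **My assumptions:** equal dropout by arm, no week-8 data from dropouts, and an unadjusted two-sample comparison at week 8.

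**1. Can the plan's 30 per arm be reproduced?** Inflating by n/(1 - 0.25):
- 10 gives 14
- 12 gives 16
- 30 gives 40
- 40 gives 54

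Multiplying by 1.25 instead gives 13, 15, 38 and 50. No stated number leads to 30. An unstated target of 22 would (22/0.75 = 29.3, rounded up to 30), as would 24 with the 1.25 multiplier.

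**2. What remains.** 60 x 0.75 = 45, or 22-23 per group. Retaining 30 would need 30/0.75 = 40 per group, 80 in total.

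**3. Half-width of the 95% interval, in SD units.** Formula: t(0.975, 2n - 2) x sqrt(2/n).
- n = 30: 0.517
- n = 23: 0.594
- n = 22: 0.608

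The interval is 15-18% wider than with 30 (0.594/0.517 = 1.15; 0.608/0.517 = 1.18).

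**4. When the lower limit is usable.** On this formula the limit is above zero only if the observed effect exceeds the half-width: about 0.6 SD at 22-23 per group and about 0.5 SD at 30. Worked cases at 22.5 per group use half-width 1.96 x sqrt(2/n + d²/(4n)) and main-trial size at 80% power, 2 x (1.96 + 0.84)²/d² per arm:
- Observed 0.5 SD: interval -0.09 to 1.09. The point estimate gives 63 per arm; the lower limit gives no finite number.
- Observed 0.8 SD: lower limit 0.19. The point estimate gives 25 per arm; the lower limit gives 423.

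**5. Probability that the lower limit is at or below zero** (noncentral t, noncentrality d x sqrt(n/2)), by assumed true effect:

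| True effect (SD) | 22.5 per group | 30 per group |
|---|---|---|
| 0.2 | 90% | 89% |
| 0.3 | 84% | 79% |
| 0.5 | 63% | 52% |
| 0.6 | 50% | 37% |
| 0.8 | 25% | 14% |
| 1.0 | 9% | 3% |

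**6. Sensitivity to baseline adjustment.** With an assumed baseline correlation r, the half-width shrinks by sqrt(1 - r²). At 22.5 per group, 1.96 x sqrt(2/22.5) = 0.584 becomes 0.51 for r = 0.5 and 0.42 for r = 0.7. The threshold in step 4 falls with it.

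**The case against.** Thirty can be read as the number randomised, and a retained target of about 22 does inflate to 30. On that reading 60 is not a miscalculation. The retained 22-23 also exceeds 12 and lies inside the cited range of 10 to 40 per group, and the primary aim is feasibility. All of this stands, and it is why the enrolment figure need not change. It does not rescue the sentence that derives the interval from at least 30 per group.

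Under intention to treat with a mixed model, children who drop out after week 4 still contribute data, so 22-23 applies mainly to week 8 and to completers. Baseline adjustment would narrow the interval, although the protocol article does not state it. Both points stand and limit the claim to the comparison assumed above.

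A reader might infer that the lower limit would usually be zero or less. The document does not support that, because it states no expected effect. The table shows the outcome is likely for true effects below about 0.5-0.6 SD and unlikely at 0.8 SD or more. Nor is dropout the main cause: at a true effect of 0.5 SD the probability is already 52% with 30 per group.

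A reader might also infer a fixed rule to power the main trial at the lower limit. The text says only that the limits can help define a plausible range, and a limit below zero can still bound such a range.

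Finally, one might see a contradiction between calling the size enough to test effects and calling it underpowered. The first sentence speaks of preliminary data and the Objectives section of preliminary effects, so this is loose wording.

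**Conclusion.** The point holds in a limited form. The justification rests on a group size that the design does not deliver at week 8 under its own dropout assumption: 22-23 per group rather than 30. For an unadjusted week-8 comparison with equal dropout, the half-width is about 0.6 SD rather than 0.52 SD. The lower limit then yields a finite sample size only if the observed effect exceeds about 0.6 SD, and about 0.5 SD even with 30 per group.

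The material does not show that 60 is too few, that a promised precision is missed (none is stated), or that the lower limit will fail whatever the true effect. Severity is minor to moderate.

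**What to change.** Keep 60 and revise the text in three places.

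- **Expected numbers.** State that 60 randomised is expected to give about 45 evaluable at week 8 (22-23 per group), with a 95% half-width of about 0.6 SD for an unadjusted standardised difference.
- **Wording.** Write of estimating effects rather than testing them, in line with the Statistical analysis section.
- **Use for the main trial.** State that its sample size will not rest on the lower confidence limit of the pilot effect. It should rest on an important SNAP difference specified in advance, the pilot SD with allowance for its uncertainty, and the retention observed.

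This changes no recruitment target, visit or treatment. The only real work is agreeing the important SNAP difference, which the main trial will need anyway.
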